## Abstract

**Background:**

Periodontal disease and lung function impairment were found to be associated with low-grade systemic or local inflammation, and it might be that gingival/periodontal inflammation triggers lung function due to systemic inflammation or the transfer of oral bacteria or its components to the lung. A recent observational study in non-smoking subjects showed that lung volumes and flow rates were significantly reduced by 71–185 ml for severe gingivitis regardless of the adjustment for potential confounders. The result did not show any confounding by smoking, and the association between gingivitis and lower lung function was not modified by systemic inflammation. The designed interventional trial primarily aims to test the hypothesis that gingivitis reduction by optimized daily oral hygiene, professional tooth cleaning and antibacterial chlorhexidine (CHX)-containing mouth rinse improves lung function in terms of forced vital capacity (FVC) by at least 2%. The secondary objective will test the hypothesis that gingivitis reduction improves forced expiratory volume in 1 s (FEV1) and forced expiratory flow at 25–75% of the pulmonary volume (FEF25-75) by at least 2%. Furthermore, the influence of the oral microbiome will be taken into account.

**Methods:**

The study has to include 120 non-smoking subjects aged between 18 and 30 years with biofilm-induced gingivitis. The chosen “waiting control group design” will compare the immediate intervention group with the delayed intervention group, which serves as a control group. Dental and gingival status, lung function and oral microbiome will be recorded. The intensified preventive intervention—professional tooth cleaning, one-stage full-mouth disinfection with CHX and safeguarding an optimal daily oral hygiene by each subject—cannot be blinded, but the outcome measurement in terms of lung function tests is blind.

**Discussion:**

This proposed multidisciplinary study has several strengths. Only one previous intervention study with patients with severe periodontitis (mostly smokers) has been performed. It is novel to include non-smoking subjects with mild and potentially reversible oral inflammation. Furthermore, this research is innovative, because it includes evidence-based interventions for gingivitis reduction, standardized measures of the outcome on lung function and oral microbiome and combines expertise from dentistry, lung physiology, oral microbiology and epidemiology/statistical modelling.

**Trial registration:**

German Clinical Trial Register DRKS00028176. Registered on February 2022.

## Administrative information

Note: The numbers in curly brackets in this protocol refer to the SPIRIT checklist item numbers. The order of the items has been modified to group similar items (see http://www.equator-network.org/reporting-guidelines/spirit-2013-statement-defining-standard-protocol-items-for-clinical-trials/).

## Introduction

### Background and rationale {6a}

Lung function has been established several decades ago as a major predictor of increased mortality later in life (as reported by [1, 13]. Accordingly, recent epidemiological studies confirmed that even mild abnormalities in lung function within the clinically normal range were associated with increased risk for mortality as well as respiratory and cardiovascular abnormalities (e.g. [13, 65]. It is also important that reductions in lung function persist during the life course [1]. Based on the increasing body of evidence of low lung function linked to detrimental effects in later life, Faner and Agusti [14] concluded that simple spirometry testing at a young age should be implemented to identify high-risk individuals. They also concluded that the identification of determinants of lung function reduction in early life is highly warranted, as well as interventions against its further impairment. Among the potential determinants of low lung function, its association with periodontal diseases (PD), such as gingivitis or periodontitis, has been investigated in a number of studies. The latest systematic review [69] identified 14 observational studies and reported a pooled odds ratio of 2.08 (95% confidence interval 1.48, 2.91) for chronic obstructive pulmonary disease (COPD). Other authors [6, 11, 19, 21, 22, 45, 60] underlined the association of oral inflammation with adverse effects on the lung, although this finding could not be supported by all studies [4, 35, 56]. However, the most recent studies [17, 20–22, 44, 61] confirmed the overall association documented in a previous systematic review (see Fig. 1). These studies were mostly restricted to PD and COPD, but a systematic review also reported a significant association between PD and asthma [41]. Smoking is known as an important co-determinant for both PD and lung diseases, and consequently, studies on PD and COPD that adjusted for smoking showed a substantial attenuation of the association [4, 21, 22]. From the observational results, it is currently uncertain to which extent smoking, as a common risk factor, is sufficient to explain the association between PD and COPD.

**Fig. 1 Fig1:**
[figure not shown]
Epidemiological findings on the associations between periodontal diseases and COPD and lower lung function in adults and potential biological mechanisms

Therefore, the results of interventional studies, which control for smoking, are essential. Until now, three interventional trials have demonstrated positive effects of periodontal therapy in patients with COPD, among them two non-randomized trials [25, 57] and a randomized trial [70]. They found improved lung function and reduced exacerbation rates in COPD patients after oral hygiene instructions and periodontal treatment (see Fig. 2). However, these studies on oral inflammation and lung health were restricted to adults in advanced age, in whom smoking already acted as a common risk factor over a long time, with local inflammation and indirect effects due to systemic inflammation as possible underlying mechanisms [34, 53] (see also Figs. 1 and 3).

**Fig. 2 Fig2:**
[figure not shown]
Interventional studies on lung function improvements and reduced COPD exacerbations in adults by reduction of periodontal diseases

**Fig. 3 Fig3:**
[figure not shown]
Potential biological mechanisms of how oral bacteria can affect the lung [18]

Regarding the details of the potential mechanisms, Linden et al. [34] stated that the inflammatory status of the airways might be affected by aspiration of dental plaque and/or haematogenous dissemination of inflammatory mediators and periodontal bacteria. In addition, a shared pathogenesis between both disorders via shared pathogens has been suggested [51]. PD is associated with low-grade systemic inflammation [16, 38, 46]. Since systemic low-grade inflammation is associated with both PD and lung function impairment [22, 52, 55, 62, 68], it may be that PD affects lung function also via systemic inflammation. As smoking is a strong determinant for both periodontal diseases [28, 30] and poor lung function, confounding has always to be taken into account, even in interventional trials. Thus, the association between periodontal diseases and lung function and/or COPD in the absence of smoking and smoking history is highly relevant. Based on this, we previously analysed the association between spirometric lung function and oral health indicators in a large group of more than 1000 non-smoking adolescents [20]. Spirometric lung volumes and flow rates were significantly reduced by 71–185 ml in the highest categories of gingivitis even after adjustment for other potential confounders in these non-smokers. This study supported the hypothesis that the reported association between poor periodontal health and low lung function is unlikely to be due to smoking alone. On the other hand, the study did not support the assumption that the association between gingivitis and lower lung function is caused by systemic inflammation, as far as indicated by the high sensitivity-C reactive protein.

It is worthwhile to mention that all presently available observational studies consistently showed lower forced expiratory volume in 1 s (FEV_1_) in the subgroups of poor oral health. However, these observations need to be interpreted with caution. Despite adjustment for several major co-factors such as smoking, socioeconomic status, chronic diseases, medication and acute infections during lung function testing, residual confounding cannot be ruled out in multifactorial processes. Moreover, all observational studies had a cross-sectional design, with the exception of one [21]. As a result of the data outlined above, there is a need for (a) interventional studies and (b) studies in younger age to validate the results obtained by Zhou et al. [70]. We combine both of these requirements in our planned study.

### Objectives {7}

The main objective is to test the hypothesis that gingivitis reduction via optimized daily oral hygiene and antibacterial chlorhexidine-containing (CHX) mouth rinsing improves lung function in terms of forced vital capacity (FVC), as an indicator of lung volume, by at least 2%. This allows interpreting the changes in lung function as direct or indirect consequences of changes in oral inflammation.

As a secondary objective, we test the hypothesis that gingivitis reduction by improved oral hygiene and CHX mouth rinsing improves forced expiratory volume in 1 s (FEV_1_) and forced expiratory flow rate at 25–75% of lung volume (FEF_25–75_), as indicators of airway obstruction, by at least 2%. Compared to the change in FVC, this will also allow to detect potential improvements regarding airway obstruction in terms of their ration FEV_1_/FVC. This is helpful for the interpretation of an improvement in lung function as a factor linked to a lower risk for obstructive airway disease.

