Observational studies could also be used for power calculation. The few studies on oral health and lung function consistently found lower lung function in subjects with periodontitis or gingivitis. A cross-sectional study in 1463 German adults aged 25 to 86 years showed FEV_1_ values lower by 5% predicted in subjects with clinical attachment loss of more than 50%, after adjustment for several co-factors. The non-smokers showed even further lowered FEV_1_, by more than 10% predicted [22]. Similarly, a prospective follow-up study of 206 subjects (mean age 42 years) found 10% lower FEV_1_ in subjects with periodontitis [21]. The third observational study of more than 650 subjects aged 50 + years from Scandinavia reported FEV_1_ values lower by 5% predicted for subjects with poor oral health [44]. The only available population-based study in younger age (15 years) showed FEV_1_ to be lower by about 20% predicted in the approximately 10% of adolescents with the highest SBI or CPI [20]. Active smoking was uncommon at this age, and the few active smokers were excluded from this analysis. Noteworthy, all five observational studies consistently showed lower FEV_1_ in subgroups of poor oral health. Despite this, some caution is needed in the interpretation. Although some of these studies included co-variates such as smoking, socioeconomic status, chronic diseases and medication, acute infections during lung function testing and early life factors, residual confounding cannot be ruled out in view of the multiplicity of potential influencing factors. Lung function has many determinants and is varying over time. This is the reason for further interventional study in subjects of younger age. Based on the critical evaluation of the study findings on oral health and lung function, we prefer a conservative approach for our power calculation.

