The power analysis focuses on the second part of the study, in which two different treatments are realized, whereby in both arms assessments before and after treatment are performed (Fig. 4). As the control treatment may be expected to be associated with a positive change, although smaller than in the target treatment group, the assumed effect is taken to be greater than zero. Thus, relative effects of m1 = 2 and of m2 = 1 are assumed for the target treatment and the control treatment group, respectively, in units that can be adapted to those of the outcome measures. There are no sufficient data on the (longitudinal) variation of measured values due to either methodological or biological sources. The power analysis is performed with an assumed variance of 1.5 for each assessment, in units identical to those of the effects and corresponding to a standard deviation (SD, square root of variance) greater than 1 but less than 1.5, which we consider as a reasonable value. Assuming that the measurement errors are independent in the pre and post-assessments, the variances add up for the pre-post differences, resulting in a total variance of each of the two differences of 3, i.e. an assumed standard deviation of about 1.7 (square root of 3) for each difference. Thus, we have two groups with expected effects of 2 or 1, both with standard deviations of about 1.7. This seems a reasonable basis for analysis, whereby the mean differences observed in the two treatment arms have to be compared in a standard 2-means comparison based on normal distributions. The comparison is performed two-sided in order to be on the safe side, although the hypothesis is that treatment arm 1 is more effective than treatment arm 2. Requiring a power of 90% (beta = 0.1, error of the second kind) at a significance level of 5% (alpha = 0.05, error of the first kind), the assumed parameter values result in sample sizes of *n* = 61 for each of the two treatment groups. When assuming variances of either 1 or 2 instead of 1.5 for each of the assessments, the required group sizes would be *n* = 42 or *n* = 84, respectively. In the latter case, a sample size of *n* = 63 in each group would still be sufficient for alpha = 0.05 at a power of 80% (beta = 0.2), which is often considered as sufficient in clinical trials. Thus, based on reasonable assumptions and conventional criteria, sample sizes of about 60 subjects per group should be adequate to perform this clinical intervention study successfully and to obtain a conclusive result.

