However, this study has also some limitations. The major limitation is related to the uncertainty about the results, because of the high novelty and the innovative characteristics of this proposed study. Due to the high methodological experience of the study group, the strong focus of an interventional study and the strong design, we believe to provide a sound answer to the underlying research question regardless of whether we could prove the primary hypothesis. (8) Finally, this trial also might have clinical implications, although the effect size of lung function changes may seem small. The power calculation of the study is based on assumed changes of 2% for FEV_1_ and FEF_25–75_ during the time of the trial. According to the available data, this is a justified and realistic assumption of short-term changes in lung function due to the oral sanitation programme. This assumed change can be considered as a conservative estimate, since real effects are more likely to be higher than smaller. From a clinical perspective, a 2% improvement in lung function per se is certainly small, but one has to put this into a lifelong scenario, considering the natural decline of lung function over time. If the improvement is not a one-time event but, at least in part, a reduction in the annual rate of decline, the resulting difference in lung function after a number of years might very well matter, particularly.

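### The primary hypothesis claims an FVC gain of at least 2%, but the planned test is of a between-arm difference against zero, sized for 2 versus 1, so significance alone would not support the claim

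*Protocol article*

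**What the plan says.** **Hypothesis.** Objectives {7} says that gingivitis reduction "improves lung function in terms of forced vital capacity (FVC), as an indicator of lung volume, by at least 2" percent. The Abstract repeats this, and the secondary objective uses the same 2% threshold for FEV1 and FEF25–75. Neither place says whether the 2% is a change within the treated arm or a difference from control.

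**Design.** Trial design {8} describes a randomised comparison of immediate with delayed intervention, the delayed group serving as control.

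**Sample size {14}.** Controls are expected to improve too, so "relative effects of m1 = 2 and of m2 = 1 are assumed for the target treatment and the control treatment group", "in units that can be adapted to those of the outcome measures". On variability: "The power analysis is performed with an assumed variance of 1.5 for each assessment", which gives each pre–post change a variance of 3 and an SD of about 1.7. The two mean changes are compared two-sided, at 5% significance and 90% power, and the hypothesis is described only as one arm doing better than the other. No 2% margin appears. The stated requirement is 61 per group, and about 60 per group is adopted.

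**Discussion.** The power calculation is described as resting on assumed 2% changes in FEV1 and FEF25–75, followed by: "This assumed change can be considered as a conservative estimate, since real effects are more likely to be higher than smaller". Neither the control arm's assumed change nor FVC is mentioned there.

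**Background evidence.** One adolescent study is described twice. In the Background (text after Fig. 3), lung volumes and flow rates were "significantly reduced by 71–185 ml in the highest categories of gingivitis". In the Sample size section, FEV1 is said "to be lower by about 20% predicted in the approximately 10% of adolescents with the highest SBI or CPI".

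**The concern.** The document describes the target effect in three ways: an FVC gain of at least 2% (Abstract, Objectives), a between-arm difference of 1 in generic units (Sample size), and 2% changes in FEV1 and FEF25–75 (Discussion). Only the second matches the randomised comparison and the stated group size.

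Rejecting a zero difference shows that the intervention does something. It does not show that the effect reaches a threshold. Here the threshold is twice the planned difference, if the units are percent. A significant result could be reported as confirming the at-least-2% hypothesis when the data fit a much smaller effect, or even exclude 2.

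**Working it through.** **Inputs** (all from Sample size {14}): assumed changes 2 and 1; variance 1.5 per assessment, so 3 per pre–post change (SD √3 = 1.732, given as about 1.7); two-sided alpha 0.05; power 90%; about 60 per group.

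**1. Reproduce the stated group size.** Normal approximation: n = 2 × SD² × (1.960 + 1.282)² / difference², where (1.960 + 1.282)² ≈ 10.51.
- Difference 1, SD 1.7: 2 × 2.89 × 10.51 = 60.7, so 61, as stated.
- Difference 1, SD √3: 2 × 3 × 10.51 = 63.0. The gap from 61 comes from rounding √3 to 1.7.
- Variance 1 or 2 per assessment: 42.03 and 84.06 (stated 42 and 84). Variance 2 at 80% power: 63 (stated 63).
- Difference 2, SD √3: 63.04 / 4 = 15.8, so 16 per group.

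The stated size therefore identifies the design effect as a between-arm difference of 1, not 2.

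**2. What counts as a positive result.** With 60 per group and SD √3:
- SE of the difference = √(3 × 2 / 60) = 0.316.
- Smallest significant difference = 1.980 × 0.316 = 0.63 (t, 118 df).
- Power at a true difference of 1 is about 88%.

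**3. A result exactly as planned.** Observed difference 1.0: 95% CI = 1.0 ± 0.63, or 0.37 to 1.63. It excludes 0 and also excludes 2.

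**4. Sensitivity to the protocol's own variance range.**

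| Variance per assessment | Smallest significant difference | 95% CI if 1.0 is observed |
|---|---|---|
| 1 | 0.51 | 0.49 to 1.51 |
| 1.5 | 0.63 | 0.37 to 1.63 |
| 2 | 0.72 | 0.28 to 1.72 |

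The conclusion is the same in each row.

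**5. What would support a between-arm gain of at least 2.** The lower 95% limit must exceed 2, so the observed difference must exceed 2 + 0.63 = 2.63. By the normal approximation (SE 0.316), the chance of this is about 1.5 × 10⁻⁷ at a true difference of 1, 2.5% at 2, 35% at 2.5 and 89% at 3. The plan proposes no such margin test; these figures only show how far the literal claim lies from the planned comparison.

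**6. The within-arm reading.** If 2% is the change in the treated arm, it equals the assumed m1 = 2. On the plan's own assumptions 1 of those 2 units also occurs in controls, so the part due to randomised treatment is 2 − 1 = 1. The planned two-arm comparison does not test the within-arm change.

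**7. Secondary point: the adolescent study.** For 185 ml to be 20% of predicted FEV1, the predicted value would have to be 185 / 0.20 = 925 ml. On an assumed predicted FEV1 of 3.5 to 4.0 L (not given in the document), 71–185 ml is 2.0–5.3% at 3.5 L and 1.8–4.6% at 4.0 L. Neither figure enters steps 1 to 5.

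**The case against.** The best defence is that 2% is meant as the change within the treated arm. The Objectives do not specify a contrast, the Discussion speaks of changes, and m1 is 2, so on that reading the numbers agree. The Sample size section also states a workable hypothesis, one arm better than the other, and its group size fits. This stands as far as it goes: there is no arithmetic error, and the formal null hypothesis could be left to an analysis plan. It does not rescue the Objectives, which attribute the whole gain to gingivitis reduction although the plan expects controls to gain as well.

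A reader might also infer more than the document supports:
- *That a positive trial could never support the claim.* It could: an observed difference above about 2.63 would put the lower limit above 2. The point is that significance alone does not.
- *That the trial is designed to detect 1%.* The units are left open. Reading one unit as one percent is an inference from the Objectives and Discussion.
- *That calling the assumption conservative is wrong.* An assumed change of 2 lies below the 3–4% predicted reported by the earlier trial and the observational differences of 5% or more cited in the same section. The label is a judgement relative to that evidence.
- *That the two accounts of the adolescent study undermine the sample size.* They are hard to reconcile, but the first covers several lung function measures and the second only FEV1, the categories may differ, and the source is not at hand. The calculation uses neither.

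**Conclusion.** The point holds as a mismatch between the stated hypothesis and the planned test. The trial is sized for a between-arm difference of 1; with 60 per group it would be positive at any observed difference above about 0.63 (0.51 to 0.72 over the protocol's variance range), and the planned result of 1.0 would exclude a between-arm gain of 2. Significance would therefore not by itself support an improvement of at least 2%. The within-arm reading makes the numbers agree but leaves a quantity that is not the randomised effect.

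The Discussion misreports the power basis: it omits the control arm's assumed change and names FEV1 and FEF25–75 instead of FVC, the variable the Objectives make primary.

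These figures rest on the protocol's assumptions of normal changes, independent pre and post errors, equal variances and 60 analysed per group. Comparing 1 unit with 2% further assumes that the units are percent. The design, group size and planned comparison are unaffected; what is at stake is the conclusion the trial may draw.

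**What to change.** 1. **Objectives and Abstract.** Restate the primary hypothesis as a difference between the immediate and delayed arms in mean FVC change, with a null value of zero. Give the planning values as 2 versus 1 (difference 1), state the units (for example percent), and report the estimate with its 95% CI. Make no at-least-2% claim from significance alone.
2. **Secondary objective.** Use the same form for FEV1 and FEF25–75.
3. **Discussion.** Describe the power basis as it stands in the Sample size section: 2 versus 1, in the stated units, for the primary variable FVC.
4. **Secondary point.** Check both accounts of the adolescent study against the source and reconcile them, saying which measure, category and adjustment each refers to.

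The cost is wording only, and the stated target becomes less impressive. If the investigators do want to claim a gain of at least 2, they would need to define a test against that margin and power it separately, which the present calculation does not do.
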